## Abstract

**Background:**

The prevalence of obesity continues to rise, and although this is a complex disease, the screening is made simply with the value of the Body Mass Index. This index only considers weight and height, being limited in portraying the multiple existing obesity phenotypes. The characterization of the chronotype and circadian system as an innovative phenotype of a patient’s form of obesity is gaining increasing importance for the development of novel and pinpointed nutritional interventions.

**Objective:**

The present study is a prospective observational controlled study conducted in Portugal, aiming to characterize the chronotype and determine its relation to the phenotype and dietary patterns of patients with obesity and healthy participants.

**Methods:**

Adults with obesity (study group) and healthy adults (control group), aged between 18 and 75, will be enrolled in this study. Data will be collected to characterize the chronotype, dietary intake, and sleep quality through validated questionnaires. Body composition will also be assessed, and blood samples will be collected to quantify circadian and metabolic biomarkers.

**Discussion:**

This study is expected to contribute to a better understanding of the impact of obesity and dietary intake on circadian biomarkers and, therefore, increase scientific evidence to help future therapeutic interventions based on chronobiology, with a particular focus on nutritional interventions.

## Introduction

1.

The prevalence of obesity continues to rise, predicted to become the biggest epidemic in history. According to the World Health Organization, around 2 billion adults are overweight; 50 million have obesity. Most of the world’s population lives in countries where obesity and overweight kill more people than underweight (1). Obesity is characterized by an excess of body fat, which can be measured by body composition analysis. Nevertheless, clinical obesity is classified based on the body mass index (BMI), expressed as the ratio of body weight in kilograms divided by the height in square meters (2, 3). Large population studies described the relationship between a higher BMI and increased mortality/morbidity risk (2, 4, 5). The BMI has been used to stratify patients into risk categories and to monitor changes in adiposity since it is an easy, affordable, and quick tool for clinical use, despite its limitations (6, 7).

Different obesity phenotypes are associated with additional cardiovascular risk (8, 9). Some of the phenotypes described in the literature are Metabolically Healthy Obesity, in which a high BMI is associated with an apparently healthy metabolic profile, lower visceral adipose tissue, high values of lean mass, and high cardiorespiratory fitness. This phenotype may transition to metabolically unhealthy obesity and is associated with an increased risk of cardiovascular diseases. Another phenotype is described as Metabolic Obesity with Normal Weight, in which individuals, despite having normal weight, present high values of visceral adipose tissue, lower insulin sensitivity, hyperinsulinemia, dyslipidemia, and increased plasma levels of pro-inflammatory cytokines. Normal weight obesity syndrome presents values of body fat mass above 30% with BMI values within the healthy range. Lastly, there is the Sarcopenic Obesity phenotype, characterized by low skeletal mass and increased fat mass percentage (10). Considering these different phenotypes, the BMI classification is insufficient to adequately stratify patients with obesity regarding types of adiposity, cardiovascular risk or adequacy of therapeutic interventions. In addition to the BMI, clinical practice guidelines suggest associating the measurement of the waist circumference as a reference for abdominal fat (11, 12), however, this measure does not differentiate subcutaneous from visceral fat deposition.

The knowledge regarding the etiology of obesity is still evolving; however, some gaps remain, since the translation of this knowledge into the treatment and management of this disease is yet to be successful in large-scale clinical programs (13). Obesity is a complex condition, therefore not to be considered a homogenous state, considering the noticeable heterogeneity observed among people that meet the current medical diagnostic criteria for obesity (BMI ≥ 30 kg/m^2^).

Obesity classes I and II encompass different health risks associated with factors that include body fat distribution, overall nutritional quality, physical activity levels, and cardiorespiratory fitness (14). Some people, although they have obesity, eat a nutritionally balanced diet and are physically active (15). Other individuals only show moderate obesity, however, when accompanied by visceral obesity, they can exhibit features of metabolic syndrome (16). These remarks underline the idea that BMI alone might not be sufficient to assess health risks, characterize, and diagnose obesity. Piché and colleagues (2) recently proposed that the singular term “obesity” does not properly define the diverse types of obesities, regarding adipose tissue type and function, body fat distribution, and patient lifestyle habits. These authors suggest that the concept of different “obesities” is more adequate to the clinical reality and to the distinct treatment challenges associated with different categories of obesity.

Current evidence indicates that there is a reciprocal interaction between metabolism and the circadian system. Primarily, a comprehensive neural network connects the suprachiasmatic nucleus (SCN) of the hypothalamus to the energetic centers implicated in, for example, food intake, sleep/wakefulness and energy expenditure (17). The effect of the circadian system on metabolism, mediated by the SCN and peripheral clocks, is reflected in the circadian fluctuations exhibited by several metabolically significant hormones (17, 18). Changes in hormonal rhythms might lead to internal malfunction and are related to metabolic dysfunctions that predispose the development of metabolic diseases such as obesity (18–22). While the SCN is mainly synchronized by light/dark cycles, peripheral clocks are entrained by feeding/fasting cycles (23, 24). Besides meal timing, nutrients can also induce phase shifts in the peripheral circadian clock. Hirao and colleagues found that a combination of carbohydrates and protein is necessary to change the mouse liver clocks (25). As reviewed by Oike and colleagues (26), nutrients such as glucose and amino acids quickly alter the expression of clock genes, particularly Per2 and Rev-erbα (27–30). Skipping breakfast or having a lower food intake in the first meal of the day alongside with high-caloric dinners impairs peripheral clock gene expression and results in higher daily glucose excursions in animals (31–33). A study conducted by Jakubowicz and colleagues on individuals with type 2 diabetes showed that calories consumed at breakfast or dinner affected the daily rhythm of postprandial glycaemic excursion and insulin levels (34). These authors also reported that skipping breakfast negatively affected clock and clock-controlled gene expression (35).

Despite the contribution in elucidating important mechanisms in chronobiology, the majority of the studies do not account for differences of circadian rhythmicity among individuals. Distinct chronotypes reflect different timings of circadian behavior, physiology, and even patterns of clock genes expression. Besides regulating sleep, the chronotype can have a major influence on appetite. Thus, the characterization of individual chronotypes (expression of circadian rhythmicity), as part of a patient phenotype, is gaining increasing importance for the development of novel and pinpointed nutritional interventions. A randomized clinical trial showed that a chronotype-adjusted diet was more effective than the traditional hypocaloric diet in the improvement of anthropometrical parameters in patients with obesity (36). Individual circadian variations may be valuable, and a critical first step, for providing information to design therapeutic strategies and to help “fine-tune” chronobiology interventions, including chrononutrition approaches (37). Research in this field is currently hindered by the fact that only a few studies assessed simultaneously the chronotype and nutrient intake and timing during the interventions. Furthermore, there is no standard method to objectively define chronotypes. Usually, this is determined by a combination of questionnaires, evaluation of clock genes expression and/or protein levels, determination of non-invasive clock outputs, such as core body temperature, and heterogeneous pools of biomarkers that act as readouts of the intrinsic circadian rhythms (38–41). Although there is an increasing interest in chronotype, as a novel dimension of nutrition and health, there is still a lack of consistent evidence regarding its relation to obesity and metabolic disturbances (42, 43). Researchers in this field highlight the need for more research and proper characterization of clock gene expression and circadian biomarkers in obesity. Furthermore, most studies have a high risk of bias and do not evaluate parameters related to metabolic dysfunction such as adiponectin, leptin, and insulin (42, 44).

The relationship between circadian rhythm disruption and obesity is complex and not fully understood. More studies are necessary to assess the role of meal schedules and dietary composition in the regulation and/or deregulation of peripheral clocks, especially including the biological differences in the circadian system through the assessment of individual chronotypes.

The present study aims to conduct an observational study on chronotype, and its relation to phenotype and dietary intake in patients with obesity, compared with healthy individuals. This study will contribute with scientific evidence to help future interventions based on chronobiology, specially chrononutrition.

## Methods and analysis

2.

### Study design

2.1.

NutriClock is a prospective observational study involving adults with obesity (study group) and healthy adults (control group). The study protocol was developed based on the Standard Protocol Items: Recommendations for Interventional Trials (SPIRIT) guidelines (45).

### Participant selection

2.2.

Participants will be recruited from healthcare centers in Leiria, Portugal. The study will also be disseminated through social networks and institutional emails, in an attempt to reach more participants.

The eligibility of the participants will be assessed on the first visit by the assessment of inclusion and exclusion criteria after the potential participants signed the informed consent. The observational study will be conducted on adults and recruitment will be gender-independent. Obesity will be defined according to the criteria of the World Health Organization (1). The detailed participant inclusion and exclusion criteria are listed in Table 1.

**Table 1 tab1:** Inclusion and exclusion criteria for the participants in both study groups.

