**Inclusion criteria**
Adults aged ≥ 18 and ≤ 75 years. BMI ≥ 30 kg/m^2^ (study group). BMI ≥ 18.5 and < 25.0 kg/m^2^ (control group).

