**Exclusion criteria**
Individuals unwilling or unable to give their informed consent. Severe psychiatric conditions and/or inability to understand and engage in the study. Night or rotating shift workers, or individuals that crossed more than two times zones in the 2 weeks before the beginning of the study. Diagnosed sleep disorders, including severe Obstructive Sleep Apnea. Pregnant women^1^. Individuals with an electronic medical device/implant^1^. Infection 4 weeks before baseline assessment. Regular use (equal to or greater than weekly) of the following medications: Wakefulness-promoting agents modafinil, amphetamine derivates, methylphenidate. Sedatives including benzodiazepines, Z-drugs (zopiclone, zolpidem and zaleplon). Melatonin, including circadian and melatonin analogs. Clonazepam and other drugs for nocturnal movement disorders. Probiotics. Anti-obesity drugs (orlistat, liraglutide). Glucocorticoids.

1 Assessment of body composition with the bioelectrical impedance analysis (BIA) equipment is not possible in these conditions.

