#### Clinical data

2.5.3.

Participants will register in the NutriClock mobile application, specifically designed for this observational study by a multidisciplinary team, including computer engineers, nutritionists, physiologists, and psychologists (53). The NutriClock mobile application and backoffice were designed and developed to comply with ethical standards and the General Data Protection Regulation. The research team and authorized healthcare professionals will have access to the information that each participant introduces in the mobile application *via* the backoffice platform.

The clinical history information may be entered voluntarily by the participant when creating the account. Participants can also add or edit information in their profile after they are registered, at any time point. Healthcare professionals can also complete the information about the participant in the NutriClock backoffice. The information that will be collected includes sociodemographic data, diagnosed pathologies, and current medication.

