#### Questionnaires

2.5.5.

To complete the participant’s characterization and data, a set of validated questionnaires and instruments will be used.

The Pittsburgh Sleep Quality Index (PSQI) is a 19-items (plus 5 additional items, in case the responder has a roommate or bed partner, that do not contribute to the total score) self-reported questionnaire, designed to subjectively assess global sleep quality based on the participant’s retrospective evaluation (considers the usual sleep habits over the past one-month period). The items of the PSQI are divided into seven components, namely, subjective sleep quality, sleep latency, sleep duration, habitual sleep efficiency, sleep disturbances, use of sleeping medication, and daytime dysfunction, each weighted equally on a scale from 0 to 3. The global PSQI score ranges from 0 to 21, corresponding to the sum of the seven components. A global PSQI score greater than 5 indicates major difficulties in at least two components or moderate difficulties in more than three components (57, 58). This instrument has been validated for the Portuguese population (59).

The Munich Chronotype Questionnaire (MCTQ) was developed by Roenneberg and colleagues to assess the circadian phase of entrainment, which is considered a quantifiable biological phenotype (41, 60). The questions aim to evaluate sleep behavior on workdays and work-free days, separately, since this distinction is essential to determine the participant’s chronotype. The chronotype resultant from the MCTQ is expressed in local time and it is based on the Mid-Sleep time in Free days (MSF) after correction for potential compensatory sleep (MSF_sc_) (60). The midpoint of sleep has been considered one of the most accurate behavioral markers to determine the circadian phase (60, 61). However, to account for the sleep debt as a cofounder, it is necessary to calculate the average sleep duration of the entire week and correct MSF by subtracting half of the oversleep. According to the results of the MCTQ database, Roenneberg and colleagues identified seven groups based on MSF_sc_, namely, extremely early, moderately early, slightly early, intermediate, slightly late, moderately late and extremely late (60). This instrument has already been validated for the Portuguese population (62).

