### Statistical analysis

2.6.

Statistical analysis will be performed using the IBM SPSS Statistics software version 28.0.1. (IBM Corp., Warrington, United Kingdom) and GraphPad Prism version 8 (GraphPad Software, Inc.; San Diego, United States). Continuous variables will be presented as the mean ± standard deviation (SD), median, and interquartile range [Q1–Q3]. Categorical variables will be presented in frequency and percentage. The normality of continuous variables will be tested using the Shapiro–Wilk test if *n* < 50 or the Kolmogorov–Smirnov test if *n* ≥ 50. Parametric tests (Independent Sample *t*-test) will be used to compare the differences between the study and the control groups if the data has a normal distribution, otherwise, non-parametric tests (Mann–Whitney *U*-tests) will be performed. According to the normality or non-normality of data distribution, Spearman’s rank-order correlation (ρ) or Pearson’s correlation coefficient (r) will be performed to calculate and assess the strength of correlations between the study variables. Statistical significance will be set at *p* < 0.05.

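### Recruitment source is neither balanced across the groups nor listed as recorded, and the group tests are unadjusted, so a difference in source could be read as an effect of obesity

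*Protocol article*

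**What the plan says.** **Routes into the study (2.2).** "Participants will be recruited from healthcare centers in Leiria, Portugal". The same paragraph adds a second route: "The study will also be disseminated through social networks and institutional emails, in an attempt to reach more participants". Neither sentence mentions cases or controls.

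**Group definition (2.2 and Table 1).** The groups are separated by BMI alone, within one age range of 18 to 75 years. On sex, the article says that "recruitment will be gender-independent". It states no matching, quota or stratification. Table 1 excludes "Night or rotating shift workers, or individuals that crossed more than two times zones in the 2 weeks before the beginning of the study", and this applies to both groups.

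**Data recorded (2.5.3).** "The information that will be collected includes sociodemographic data, diagnosed pathologies, and current medication". Recruitment source is not in that list. Participants enter their clinical history voluntarily, and healthcare professionals may complete it.

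**Chronotype measure (2.5.5).** Of the Munich questionnaire the article says: "The questions aim to evaluate sleep behavior on workdays and work-free days, separately, since this distinction is essential to determine the participant’s chronotype". Chronotype is mid-sleep on free days, corrected for sleep debt (MSFsc).

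**Analysis (2.6).** Independent-samples t-tests, or Mann–Whitney tests if the data are not normal, "will be used to compare the differences between the study and the control groups". Associations are assessed by simple correlations. No covariate is named.

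**The concern.** Healthcare centres reach people in contact with care. Institutional e-mail and social networks probably reach more people who are employed or studying. That description is an inference from the nature of the routes, not a statement in the article. If it is right, and if the two groups end up with different mixes of the routes, they will also differ in work or study status, and so in when people get up, eat and sleep.

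The study compares obesity and control on outcomes of that kind: time of first and last meal, overnight fasting period, PSQI and MSFsc. An unadjusted test would credit any such difference to obesity.

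A covariate can be added to an analysis later, but a source that was never recorded cannot be recovered. This is why the point belongs in the protocol and cannot be left wholly to the analysis stage.

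**Working it through.** **1. What the plan's own figures fix.** The article gives no figure for confounding by source. It does give the group sizes. From 2.3, with p0 = 0.18 and p1 = 0.55:

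n = (0.18 × 0.82 + 0.55 × 0.45) × (1.96 + 0.84)² / (0.55 − 0.18)² = 0.3951 × 7.84 / 0.1369 = 22.63, rounded up to 23 per group.

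This reproduces the stated 23. The article then plans to enrol 32 per group. Both sizes are used below.

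**2. Inputs that must be assumed.** The article gives neither the share of each group recruited online nor any outcome by route. The assumptions are:

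- s, the difference between the groups in the share recruited online: 0.20, 0.40 or 0.60, placed symmetrically around one half (for s = 0.40, one group has 30% and the other 70%);
- d, the difference in an outcome between the routes, in units of the within-route SD: 0.3, 0.5 or 0.8;
- no true effect of obesity.

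**3. Formulas.**

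- Spurious group difference: b = s × d.
- Variance within each group: v = 1 + (0.5 − s/2)(0.5 + s/2) d².
- Standard error: SE = √(2v/n).
- Rejection probability of a two-sided 5% test (normal approximation): 1 − Φ(1.96 − b/SE) + Φ(−1.96 − b/SE).

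**4. Middle case at 32 per group.** With s = 0.40 and d = 0.5:

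- b = 0.20 SD;
- v = 1 + 0.3 × 0.7 × 0.25 = 1.0525;
- SE = √(2 × 1.0525 / 32) = 0.256;
- b/SE = 0.78;
- rejection probability 12.2%.

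**5. Full range.**

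| s | d (SD) | b (SD) | Rejection, 23 per group | Rejection, 32 per group |
|---|---|---|---|---|
| 0.20 | 0.3 | 0.06 | 5.5% | 5.6% |
| 0.20 | 0.5 | 0.10 | 6.3% | 6.7% |
| 0.20 | 0.8 | 0.16 | 8.0% | 9.2% |
| 0.40 | 0.3 | 0.12 | 6.9% | 7.6% |
| 0.40 | 0.5 | 0.20 | 10.1% | 12.2% |
| 0.40 | 0.8 | 0.32 | 17.5% | 22.5% |
| 0.60 | 0.3 | 0.18 | 9.3% | 11.0% |
| 0.60 | 0.5 | 0.30 | 16.9% | 21.8% |
| 0.60 | 0.8 | 0.48 | 34.1% | 44.8% |

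The bias does not shrink as the sample grows. The larger group size only makes it more likely to reach significance.

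**6. Which outcomes are exposed.** The table is in SD units and applies to any continuous outcome, but d need not be the same for all of them. MSFsc uses free-day sleep and corrects for sleep debt, so much of the work schedule's influence is removed by construction, and smaller values of d are the more natural reading. The article describes no such correction for meal times, which come from a 3-day diary begun on the day of Visit 2, or for PSQI, which covers usual sleep over the past month. For these two, d has no built-in limit apart from the exclusion of shift workers.

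**The case against.** The strongest objection is that the article never says the groups come from different places. Section 2.2 opens both routes to everyone, and 2.4 invites all potential participants. A reader might infer that patients with obesity will come from healthcare centres and normal-weight controls from e-mail and social media. That is possible, but the documents do not support it as a fact about the plan. This part of the objection stands in full.

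A reader might also infer that nothing in the plan guards against differences in schedule. That is wrong as well. Night and rotating shift workers are excluded, sociodemographic data are collected and may include occupation, MSFsc is built to reduce the effect of work schedule, and 2.5.4 allows a paper diary for people who do not use a smartphone. These safeguards narrow the problem without closing it. Shift exclusion leaves ordinary differences between employees, students and people not working. The MSFsc correction does not extend to meal times or PSQI. Collected data help only if they are complete and used in the comparison.

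On size, stronger inputs give a more alarming figure. Suppose online recruits make up 60% of controls and 20% of cases and have MSFsc 0.5–1.5 h later, with an SD of 1.0–1.2 h. The spurious difference is then 0.2–0.6 h, and 10–66% of studies with 32 per group would be falsely significant. None of these inputs is in the article, and such shifts sit poorly with a measure corrected for work-related sleep debt, so this range should not be relied on.

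Finally, a strict quota by route would work against a study that already expects difficulty in recruiting (Section 3). Restricting the analysis to healthcare-centre recruits would not settle the matter either. With the same assumed shares, 32 × 0.8 ≈ 26 cases and 32 × 0.4 ≈ 13 controls would remain, with power of about 30% for a 0.5 SD difference. Both points stand, and the fix avoids both measures.

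**Conclusion.** The concern holds in a limited form. Three features of the article combine: two recruitment routes with no link to or balance across the groups, no listed record of the route, and unadjusted tests between unmatched groups. If the groups differ in source, the difference passes directly into the comparison of obesity with control, chiefly for meal times and PSQI and to a lesser degree for MSFsc.

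Whether the groups will differ in source is unknown, and the amount of bias cannot be derived from the article. Under the assumptions shown, the false-positive rate at 32 per group runs from about 6%, which is negligible, to about 45%, with about 12% at the middle values, against a nominal 5%. These figures illustrate what the plan leaves open and do not predict the result. The change is worth making because it is cheap and because the missing information cannot be obtained afterwards.

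**What to change.** - **Visit 1 form.** Record recruitment source (healthcare centre, or social network/institutional e-mail) and working status (employed, student, not working) for every participant. Ask both directly, without relying on voluntary entry in the app. Report both by group.
- **Section 2.2.** State that both groups will be advertised for through both routes. Do not set a hard quota.
- **Section 2.6.** Keep the unadjusted tests. Add a regression-based group comparison of MSFsc, PSQI and meal times, adjusted for working status, age and sex. Add recruitment source to that model as a sensitivity analysis. Source is better placed there than in the main adjusted model because obesity may itself bring people into contact with healthcare centres. If source and group turn out to be closely tied, the estimate will be imprecise and should be reported as such.

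**Cost.** Two form fields, one extra analysis and a few degrees of freedom: two for working status, one each for age and sex, and one more for source in the sensitivity model.
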